Another risk factor for mental health is the individual adaptation to a new life in the host country. Heslehurst et al. (2018) reported daily difficulties faced by immigrants and asylum seekers in the host country: not knowing the language and being unfamiliar with the local lifestyle and health practices can create additional burdens and risks for mental and general health. Systematic reviews report that perinatal outcomes such as mental health, maternal mortality, preterm birth and congenital anomalies are predominantly more severe among migrant women (Falah-Hassani et al., 2015: Heslehurst et al., 2018). In a German study, 87.4% of the pre-and postpartum migrants were affected by medical complications or high-risk pregnancies (Kaufmann et al., 2022). However, these studies often do not distinguish among the different statuses of migrant (refugee vs. immigrant) populations, and host countries that may significantly differ regarding the organization of access to support and health care services. For example, an Australian study (Snow et al., 2021) showed elevated psychosocial risk factors among women of refugee background compared with Australia born-women, with the possible under-reporting of mental health problems and family violence. Research on healthcare for pre-, peri- and postpartum refugee women in high-income countries has shown that their access to health care is hampered by immigration experiences, insufficient health literacy, poor language skills, insufficient perception of health needs and use of health services, and legal restrictions (Haith-Cooper and Bradshaw, 2013; Rizkalla et al., 2020). These results raise questions regarding assessing psychosocial risk within different cultural groups and show the importance of the culture-sensitive approach to women with different cultural backgrounds. A systematic review and meta-analysis showed that the prevalence of current PTSD among migrants exposed to armed conflict is 31%, the current major depressive disorder is 25%, and the prevalence of generalized anxiety disorder is 14% (Mesa-Vieira et al., 2022). Migrating to a middle-income or low-income country was associated with an increased prevalence of generalized anxiety disorder—however, evidence is still scarce (Fellmeth et al., 2018).

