### Sample size

No restrictions have been put in place for participant registration. Nevertheless, the sample size was determined by taking into account the number of newborns in Ukraine. Consequently, a minimum sample size of 300 individuals will be recruited using a significance level of α-level of 0.05 and variability of 50%. It is essential to bear in mind, though, that the ongoing war situation, which includes the lack of electricity in Ukraine, the possibility of people evacuating cities, and missiles, may make it challenging to reach this sample size.

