#### Psychometric properties

To examine the psychometric properties of the questionnaires in the Ukrainian language, several analyses will be reported. Exploratory Factor Analyses (EFA) will be conducted using Statistical Package for the Social Sciences (SPSS), Version 26 software. Analysis of the factor dimensional constraints will determine each model’s underlying individual item loadings. Based on the results of the EFA, Confirmatory Factor Analysis (CFA) will then be analyzed. ECA will be used to analyze how to fit the models using several indexes such as Satorra-Bentler χ^2^, CFI, RMSEA and the confidence interval of RMSEA statistics will be calculated. Lagrange multipliers and Wald test will be sequentially performed to improve the models’ fitness, following the study’s hypotheses. Standardized coefficients and measurement equations with scores in R2 will be reported. These analyses will be conducted using the AMOS program.

Prediction models. To examine the risk and protective factors associated with perinatal mental health outcomes, a random sample of 70% of participants will be used to derive the machine learning algorithms, including regularized logistic regression, random forest, decision tree, and gradient boosting to predict the risk of perinatal mental health outcomes, and their performance, and the remaining 30% for validation. First, in the derivation sample, all predictors described above will be included in the models to estimate the probability of depression, anxiety, or PTSD. Beginning with a model containing all potential covariates, the variable with the least significant *p* value will be removed and tested using the likelihood-ratio test until all variables left in the model significantly (at alpha = 0.05) contributed to the model.

In regularized logistic regression models, results will be presented as Odds Ratio (OR) with 95% confidence intervals (CIs).

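### At the stated minimum of 300 women, the single random 70/30 split leaves 90 women to validate the prediction models and withholds 30% of the events from fitting

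*Protocol article*

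**What the plan says.** The prediction-model paragraph of the protocol article (under Data analysis, Psychometric properties) fixes one division of the sample: "a random sample of 70% of participants will be used to derive the machine learning algorithms", "and the remaining 30% for validation". The algorithms are listed as "including regularized logistic regression, random forest, decision tree, and gradient boosting to predict the risk", and the outcomes are depression, anxiety or PTSD. Variable selection by p-value follows in the derivation part. The paragraph mentions no repetition of the split, no cross-validation and no bootstrap. The next paragraph adds a forward stepwise logistic regression, an R² and ROC curves with AUC, among several aspects of model performance.

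The Sample size section says that "a minimum sample size of 300 individuals will be recruited using a significance level of α-level of 0.05 and variability of 50" per cent. It also says that "No restrictions have been put in place for participant registration", so 300 is a floor, but it warns that the war "may make it challenging to reach this sample size". No event count or precision is set for the prediction models.

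The article gives no design assumption for event rates. Its Introduction reports background figures from a meta-analysis: "the prevalence of current PTSD among migrants exposed to armed conflict is 31%, the current major depressive disorder is 25" per cent, with generalized anxiety disorder at 14%. It also cites 28.2% at high risk of postpartum depression in war-affected Syria and 34.8% PTSD in internally displaced pregnant women.

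**The concern.** A single random hold-out pays twice. The models are fitted on fewer events than the study collects, and their performance is then measured on a set too small to measure it well. A different random draw would give different estimates and could change which of the four algorithms looks best. One of the study's main goals is to identify risk and protective factors, and the plan starts from all candidate predictors and removes them by p-value. That kind of selection becomes less stable as events are given up. What is at stake is the reliability of the selected predictors and of the reported performance.

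**Working it through.** **The plan's own figure.** For a single proportion, n = 1.96² × p(1 − p) / e². With p = 0.5, e = 5% gives 385 and e = 6% gives 267. A sample of 300 corresponds to e = 5.66%. The margin is not stated, so 300 can be neither confirmed nor refuted; it is taken as given below. It was not derived for prediction models.

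**Split.** 0.70 × 300 = 210 for derivation; 0.30 × 300 = 90 for validation.

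**Events and precision.** Events are women × prevalence. The standard error of an AUC, A, with m cases and n non-cases (Hanley-McNeil) is

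SE² = [A(1 − A) + (m − 1)(Q₁ − A²) + (n − 1)(Q₂ − A²)] / (mn), with Q₁ = A/(2 − A) and Q₂ = 2A²/(1 + A).

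At an assumed A = 0.75: A(1 − A) = 0.1875, Q₁ − A² = 0.6000 − 0.5625 = 0.0375, Q₂ − A² = 0.6429 − 0.5625 = 0.0804.

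Example with 13 cases and 77 non-cases: (0.1875 + 12 × 0.0375 + 76 × 0.0804) / 1001 = 0.00674, so SE = 0.082 and the half-width is 1.96 × 0.082 = 0.16.

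| Event rate (source) | Cases in 90 | 95% CI at AUC 0.75 | Half-width |
|---|---|---|---|
| 14% (anxiety, Introduction) | 13 | 0.59–0.91 | 0.16 |
| 25% (depression, Introduction) | 22 | 0.62–0.88 | 0.13 |
| 28.2% (Syrian study, Introduction) | 25 | 0.63–0.87 | 0.12 |
| 31% (PTSD, Introduction) | 28 | 0.63–0.87 | 0.12 |
| 34.8% (displaced pregnant women, Introduction) | 31 | 0.64–0.86 | 0.11 |
| 50% (upper case, assumed) | 45 | 0.65–0.85 | 0.10 |

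**Comparing two algorithms on the same 90 women.** The comparison is paired, so SE of the difference = SE × √(2(1 − r)), where r is the correlation between the two AUC estimates (assumed). At r = 0.8:

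- 13 cases: SE 0.052, half-width 0.10, difference detectable with 80% power 0.145, power for a true difference of 0.05 about 16%.
- 28 cases: SE 0.037, half-width 0.07, detectable difference 0.105, power for 0.05 about 27%.
- 45 cases: half-width 0.06, detectable difference 0.09.

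At r = 0.9 the power for a difference of 0.05 is still at most 47% with 28 cases. In a binormal simulation (score correlation 0.5 to 0.8 within cases and non-cases), models with true AUCs of 0.75 and 0.70 come out in the wrong order in roughly 10% to 27% of splits. Four equally good models differ from best to worst by 0.05 to 0.11 on average through chance alone.

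**Events given up in fitting, and precision if all 300 are used.**

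| Event rate | Events in 210 | Events in 300 | Half-width on 90 | Half-width on 300 |
|---|---|---|---|---|
| 14% | 29 | 42 | 0.16 | 0.09 |
| 25% | 52 | 75 | 0.13 | 0.07 |
| 31% | 65 | 93 | 0.12 | 0.06 |

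The gain in events is 300/210 = 1.43, that is 43% more. The last column treats a resampled AUC as about as precise as an AUC on 300 women, which is an approximation.

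**What a 30% hold-out would need.** For a half-width of 0.05 at AUC 0.75, validation needs about 950, 572 or 483 women at 14%, 25% or 31%. Divided by 0.30, that is about 3,170, 1,910 or 1,610 women in total.

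**The case against.** *300 is only a floor.* True: registration is uncapped and the hold-out could be larger. But the article names no higher target and warns that even 300 may not be reached.

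*The event rates are proxies.* Also true. The 14% to 31% are diagnosed disorders in conflict-exposed migrants, whereas this study counts women above self-report cut-offs, which may give more cases. The 14% figure, which drives the widest interval, is the weakest. The conclusion does not depend on it: 28.2% and 34.8% give 25 and 31 cases, and 45 cases still leave about ±0.10.

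*Ranking is not stated.* The article fits four algorithms and refers to their performance, but nowhere says that a winner will be chosen; its stated purpose is to examine risk and protective factors. The imprecision and the lost events remain without any ranking.

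Three stronger readings are tempting and not supported. A reader might infer that a useful model and a weak one cannot be told apart. That goes too far: the comparison is paired, gaps of about 0.10 to 0.15 are detectable, and even with 13 cases the interval for an AUC of 0.75 excludes 0.5. A reader might infer that AUC is the sole performance criterion. The article announces several aspects of performance, lists R² and adds AUC, in a paragraph that opens with the stepwise regression. A reader might also fault a random split for not testing whether the models carry over between Ukraine and the host countries. The article makes no such claim for it.

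*Resampling would not settle close comparisons either.* This stands. With all 300 and r = 0.8, the half-width for a difference between two AUCs is still about 0.06 (14%) to 0.04 (31%).

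**Conclusion.** The point holds as an avoidable inefficiency in a method that the article fixes, not as something it merely leaves unsaid. At the minimum of 300 women, one random hold-out measures an AUC of 0.75 to within about ±0.16 to ±0.12, or ±0.10 at best if half the women are cases. The result depends on the draw, and differences of about 0.05 between algorithms cannot be resolved. Thirty per cent of the events do not contribute to fitting.

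The split and the count of 90 come from the text. The case counts rest on background prevalences, and the intervals on an assumed AUC of 0.75. The between-model figures also rest on an assumed correlation. A sample well above 300 would narrow the intervals, but the share withheld from fitting would stay at 30%. The change is worth making because it is cheap; it does not mean that the planned models would be uninformative.

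**What to change.** Replace the 70/30 split. Develop each model on all women, and estimate its performance, including AUC, by repeated 10-fold cross-validation or by at least 500 bootstrap samples, corrected for optimism. Every data-driven step must be repeated within each resample: tuning of the algorithms, the p-value elimination and the stepwise selection. Otherwise the correction is too small. Report the corrected estimates with their uncertainty, and do not interpret AUC differences of about 0.05 as showing that one algorithm is better.

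The change needs revised wording and more computing time, but no further recruitment or data. Its downside is that no untouched hold-out set remains, so the credibility of the estimates rests on the resampling being done in full.

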### Assessment, care, and trust—In pregnant and new mothers

This questionnaire includes 40 questions to record sociodemographic data, including current residence, education, number of prior pregnancies, the number of biological children (including miscarriages), the number of individuals residing in their home (adults and children), marital status, whether they are living with a partner, basic information concerning the location after the war outbreak and access to support, changes since the beginning of the war, exposure to armed-conflict or limitations to medical support and social support. This questionnaire was created for this study.

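### If the 40 questionnaire items and five personality scores enter as separate terms, elimination from all covariates in about 210 women would leave about 3 to 5 spurious factors per model; fix a short candidate list

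*Protocol article*

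**What the plan says.** The prediction-model text in the protocol article (Data analysis, under Psychometric properties) fixes three things.

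- **Derivation sample:** "a random sample of 70% of participants will be used to derive the machine learning algorithms", with the rest kept for validation.
- **Starting model:** "First, in the derivation sample, all predictors described above will be included in the models".
- **Elimination:** "Beginning with a model containing all potential covariates, the variable with the least significant" p value is dropped, with a likelihood-ratio test, until every remaining variable is significant at 0.05.

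The algorithms named include regularised logistic regression.

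Most candidate predictors come from the purpose-built form (Assessment, care, and trust): "This questionnaire includes 40 questions to record sociodemographic data" and further topics. No scoring is given. Table 1 groups the form into seven distinct predictor constructs. The Ten-item personality inventory section adds five trait scores. Table 1 lists personality under outcomes, but the Abstract and the objectives treat it as a protective or risk factor.

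Under Sample size, "a minimum sample size of 300 individuals will be recruited". That figure is a floor ("No restrictions have been put in place for participant registration"), and the same section warns that the war "may make it challenging to reach this sample size".

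**The concern.** The minimum of 300 rests on an alpha level and a 50% proportion. It does not take account of how many predictors enter the models or how many cases are expected. The chi-square reference for a likelihood-ratio test is a large-sample result, and it fails when there are only one or two cases per estimated term. When one outcome is rare, the unpenalised starting model may also have no finite maximum-likelihood solution. Finally, the more candidate terms are tested at 0.05, the more null factors survive.

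Finding risk and protective factors is one of the study's main goals, and the results are meant for policymakers. Spurious factors in the final models would bear directly on that goal.

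**Working it through.** **1. The plan's own figure.** For one proportion, n = z²p(1−p)/e², with p = 0.50 and two-sided alpha 0.05 (the article does not state sidedness). A margin e of 5 points gives 385, 6 points gives 267, and 300 needs about 5.66 points. No margin is stated, so 300 can be neither confirmed nor refuted. It is not a calculation for the prediction models in any case.

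**2. Cases in the derivation sample.** 0.70 × 300 = 210. At the rates cited in the Introduction:

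- anxiety, 14%: 210 × 0.14 = 29.4
- depression, 25%: 210 × 0.25 = 52.5
- PTSD, 31%: 210 × 0.31 = 65.1
- PTSD in internally displaced pregnant women, 34.8%: 210 × 0.348 = 73.1

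**3. Cases per term.** The number of terms is an assumption, because the article does not give it.

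- Item-level entry, 40 + 5 = 45 terms before any dummy coding: 29.4/45 = 0.65 to 73.1/45 = 1.62.
- One score per Table 1 construct plus five traits, 7 + 5 = 12 terms: 29.4/12 = 2.45 to 73.1/12 = 6.09.

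**4. The full model, before anything is removed.** Unpenalised logistic regression was simulated at n = 210 with 1,500 samples per setting. Half the predictors were binary and half continuous, with mild common correlation and five weak true effects. One null predictor was tested at chi-square 3.84, and existence of a finite fit was checked by linear programming.

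| Terms | Prevalence | Null rejected at nominal 5% | No finite fit |
|---|---|---|---|
| 12 | 14% | 5.3% | 2.3% |
| 12 | 34.8% | 7.0% | under 0.1% |
| 45 | 14% | 12.9% | 13% |
| 45 | 25% | 12.1% | 1% |
| 45 | 34.8% | 7.7% | under 0.1% |
| 60 | 14% | 15.8% | 41% |
| 60 | 34.8% | 11.5% | 0.1% |

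The Monte Carlo standard error at 12.9% is √(0.129 × 0.871/1500) = 0.9 points. Across all sets of runs with 45 terms at the cited rates, rejection lay between roughly 7% and 17%.

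**5. After elimination.** The backward rule was then run to its end (n = 210, 300 samples per setting, four true effects at log odds ratio 0.4). Share of null predictors retained:

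| Starting terms | 14% | 25% | 31% | 34.8% |
|---|---|---|---|---|
| 45 | 12.7% | 7.4% | 7.2% | 7.2% |
| 12 | 6.9% | 6.3% | 6.0% | 5.9% |

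In counts, 45 starting terms include 41 nulls: 41 × 0.072 = 3.0 spurious factors at the favourable end and 41 × 0.127 = 5.2 at 14% prevalence. Twelve starting terms include 8 nulls: 8 × 0.063 = 0.5. A further simulation at the same size with 45 terms agreed: about 3 to 5.5 null factors in the final model beside 2 to 3 true ones, against about 0.5 null factors with 12 terms.

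**6. Higher prevalence or a larger sample.** At 50% prevalence, with 600 samples per setting and a simulation error of about 2.5 points, a null predictor in the full model still passed in about 10% of samples with 45 terms and 13% with 60. With 300 women in derivation (300/0.70, about 430 in total), the rate with 45 terms was still 7% to 11%.

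**The case against.** The strongest objection is that the term count drives the result and the article does not state it. Forty questions are not forty covariates. The only list headed as predictors is Table 1, with seven constructs. One score for each, plus five traits, gives about 12 terms, and the problem then nearly vanishes. How items become scores is also detail that a condensed article may leave to a fuller plan. This stands, and it makes the point conditional. It does not remove it: the article prescribes the starting model as everything available, and nothing in it limits entry to one score per construct.

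Second, elimination judges the final terms in a much smaller model, so most of the full-model inflation does not reach the reported result except near 14% prevalence. This also stands. The surplus of spurious factors at higher prevalence comes mainly from the number of terms tested.

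Third, the cited rates are not the study's own expected rates. The screening cut-offs on its scales may flag more women, and enrolment is not capped at 300. Either would ease the problem. Neither brings the full-model test back to 5% in the runs above, and the article itself warns that 300 may not be reached.

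Fourth, regularised regression is already named. A penalised fit does stay finite, but a likelihood-ratio test on it has no chi-square reference, so the penalty does not rescue the elimination rule.

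A reader might go further and infer that the reported factors would be chiefly chance findings, or that the models would predict badly in new women. The documents do not support either. Real factors are retained alongside the spurious ones. Predictive performance of an unpenalised full model says little about a plan that names a penalty and holds back 30% for validation.

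**Conclusion.** The point holds conditionally. If the form is entered item by item with the personality scores (about 45 terms) in 210 women, the nominal 5% test of a null factor in the full model rejects in roughly 7% to 17% of samples. After elimination about 7% to 8% of null factors are retained (about 13% at 14% prevalence), which is about 3 to 5 spurious factors beside 2 to 3 real ones. With about 12 terms, rejection is 5% to 7% and about 0.5 spurious factors remain.

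The lack of a finite fit should be claimed only for a low-prevalence outcome: about 13% of samples at 14% prevalence, and about 1% or less at 25% and above. It would be wrong to read it as a general failure of the models.

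The figures assume exactly 300 women, the prevalences cited in the Introduction, and the simulated predictor mix and effect sizes. Dummy coding beyond 45 terms makes matters worse; more women or more cases make them better.

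**What to change.** In the prediction-model text, replace the all-covariates start with a candidate list fixed before outcomes are examined: one score per Table 1 predictor domain, the personality scores, and a few background variables, about 12 to 20 terms in all. State how each domain score is formed from the questionnaire. Settle whether personality is a predictor or an outcome; this changes the count by only five.

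Fit that list once per outcome with the penalised logistic regression the plan already names, in place of elimination by likelihood-ratio test. The following paragraph describes a forward procedure for logistic regression, and the new wording should cover that as well.

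The cost is analysis-plan wording and the work of defining the domain scores; no new data are needed. The downside is that associations of single questionnaire items become descriptive only.

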## Abstract

**Background:**

The aim of the Perinatal Mental Health for Refugee Women (PMH-RW) Project is to investigate the impact of the war on perinatal mental health: anxiety, post-traumatic stress, depression, and birth trauma symptoms. It will also evaluate the factors that serve as protective elements for the development of these potential diagnoses (such as personality traits, social support, sociodemographic characteristics, and access to medical/mental health services).

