### Symptoms

Another objective is to evaluate possible risk and protective factors (including social and economic factors, personality traits, social support, and access to medical/mental health services). We are focusing on the two groups of women who were affected by war during pregnancy: those who left Ukraine and are now refugees in other European countries (known as external refugees) and those who chose to remain in Ukraine (in the same place of residence, considered as internal refugees).

The main goals are the following:To evaluate how perinatal mental health has been affected during the war, by observing the differences in (a) levels of depression, anxiety, post-traumatic stress disorder, and birth trauma; as well as in (b) clinical risk indices (proportion of women above the clinical cut-off point on a validated self-report scale)To research which risk and protective factors have a bearing on perinatal mental health during the war.To examine the links between pregnancy results and mental health of women in war-affected areas.To examine the experiences during the birth and delivery, specifically the potential traumatic events during this period.To assess the perinatal women’s needs concerning support and mental health services in Ukraine and in the host countries.

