### Participants

The research sample consists of females in the time around childbirth. To be included in the study at the beginning, participants must meet the following criteria:Being pregnant or a biological mother of an infant up to 12 months of age.Being 18 years or older.Being a war refugee from Ukraine (entrance to EU countries from 24 February 2022) or staying in Ukraine after/during the war.Consenting to take part in the study.

The exclusion criteria are:Not being currently pregnant or not being the biological mother of an infant up to 12 months of age.Younger than 18 years of age.Not consenting to take part in the study.

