**Independent/predictor**		
Social support	ACT-PNM	NA
Coping strategies	ACT-PNM	NA
Emotional impact	ACT-PNM	NA
War exposure	ACT-PNM	NA
Pregnancy outcome (birthweight, preterm birth, complications?)	ACT-PNM	NA
Health background/ earlier mental health, substance use,	ACT-PNM	NA
access to the perinatal health services	ACT-PNM	NA
Pregnancy outcome (birthweight, preterm birth, complications?)	ACT-PNM	NA

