**Dependent/outcomes**		
Depression symptoms	EPDS	Cox et al. (1987)
Anxiety symptoms	GAD-7	Spitzer et al. (2006)
PTSD symptoms	IES-R	Weiss and Marmar (1997)
Birth PTSD	City BiTS	Ayers et al. (2018)
Personality	The 10-item personality inventory (TIPI)	Gosling et al. (2003)

NA = Not Applicable.

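### Table 1 lists personality as an outcome, and birthweight and preterm birth as predictors in a sample that includes women still pregnant; the prediction models inherit both roles

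*Protocol article*

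**What the plan says.** Table 1 of the protocol article sorts the variables into two blocks.

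- The Independent/predictor block contains "Pregnancy outcome (birthweight, preterm birth, complications", followed by a question mark. The row is printed twice. The same block contains "Emotional impact", with the study's own questionnaire (ACT-PNM) as source.
- The Dependent/outcomes block ends with "The 10-item personality inventory (TIPI"), after the scales for depression, anxiety, PTSD and birth-related PTSD.

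Elsewhere the article gives personality a different role. The Abstract (Background) counts it among the "protective elements for the development of these potential diagnoses (such as personality traits"), and the objective in the Symptoms section is to evaluate "possible risk and protective factors (including social and economic factors, personality traits, social support, and access to medical/mental health services").

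The first inclusion criterion (Participants) is "Being pregnant or a biological mother of an infant up to 12 months of age".

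For the prediction models (Data analysis, under Psychometric properties), a random 70% of participants forms the derivation sample, in which "all predictors described above will be included in the models to estimate the probability of depression, anxiety, or PTSD". No exception by perinatal stage is given. A further paragraph plans forward-stepwise logistic regression for the study's dependent variables and says that this method predicts a dichotomous variable.

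**The concern.** The second goal, on risk and protective factors, depends on these models, and the models take their variables from roles that do not fit the study.

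**Personality.** With TIPI in the outcome block, the five traits are not among the predictors. The Introduction calls neuroticism a well-established risk factor in peacetime and says that little is known about its role in war-affected populations. A question the authors raise themselves could therefore drop out of the analysis meant to answer it.

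**Birth variables.** Birthweight and preterm birth of the current pregnancy are undefined for a woman who is still pregnant. This is not ordinary missing data, because no value exists to be recovered. Variable elimination starts from the model with all covariates. Under complete-case fitting, the birth variables would therefore fix which women are analysed at the first step. The results would describe postpartum women but be reported as perinatal.

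**Working it through.** **1. Personality: the statements side by side**

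| Place | Role of personality |
|---|---|
| Abstract, Background | Protective element |
| Introduction | Neuroticism an established risk factor in peacetime |
| Symptoms (objective) | Risk or protective factor |
| Table 1 | Dependent variable/outcome |

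The first three agree and Table 1 contradicts them. The effect differs between the two modelling paragraphs:

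- *Prediction models.* The targets are depression, anxiety or PTSD, so personality is not modelled as an outcome here. The fault is that, by Table 1, it is not a predictor either.
- *Forward logistic regression.* The targets are the dependent variables, which by Table 1 include TIPI. The Ten-item personality inventory section describes five subscales scored 2 to 14 and gives no cut-off, so they are not dichotomous as that paragraph requires.

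**2. Birth variables: what a pooled model can do**

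Pregnant women are eligible, birthweight and preterm birth are predictors, and all predictors enter. For a woman still pregnant there are three options: exclude her, impute a birth that has not happened, or code the variables as not applicable. The article describes none of these.

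**3. Scale under complete-case fitting**

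Inputs from the article: minimum sample 300 (Sample size), 70% derivation and 30% validation (prediction models). The 300 cannot be strictly reproduced because no margin of error is given. With variability 50% and alpha 0.05 it corresponds to 1.96 × √(0.25/300) = 0.0566, or 5.66%. Nothing below depends on this.

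Assumptions: complete-case fitting, and a pregnant share s, which the article does not state.

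- Derivation: 0.7 × 300 = 210, leaving 210 × (1 − s)
- Validation: 0.3 × 300 = 90, leaving 90 × (1 − s)

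| s (assumed) | Total | Derivation | Validation |
|---|---|---|---|
| 0% | 300 | 210 | 90 |
| 20% | 240 | 168 | 72 |
| 50% | 150 | 105 | 45 |
| 60% | 120 | 84 | 36 |

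For a sense of the event count, take the 25% prevalence of major depressive disorder that the Introduction cites for conflict-exposed migrants. This is not a perinatal screening rate and is used only as an assumption. Derivation events would be 0.25 × 210 = 52.5 with everyone included, 0.25 × 168 = 42 at s = 20%, and 0.25 × 84 = 21 at s = 60%.

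**The case against.** **The models need not follow Table 1.** The rule refers to predictors described earlier, and the Abstract and objective also come earlier. Leaving personality out is therefore one reading, not a stated exclusion. The forward-regression paragraph also speaks of clinical outcomes, so modelling TIPI as a target may be an over-literal reading of a misplaced row. This stands as far as intent goes. It does not remove the contradiction, and Table 1 is the only place that assigns roles.

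**Pregnant women need not be lost.** A not-applicable level or an interaction with stage would keep them in, some implementations of tree methods accept missing values, and such handling may be set out in a fuller plan. This stands against any claim that they will be dropped, so the loss figures are conditional. It does not answer the point that the stated rule puts all predictors into a model with no split by stage.

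**Birth variables are there on purpose.** The third goal links pregnancy results with mental health. That is true, and a postpartum-only model serves it. Complications can also arise during pregnancy, and earlier pregnancies could be meant, so the problem is exact only for birthweight and preterm birth of the current pregnancy.

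**Follow-up could supply the births.** The Introduction speaks of a longitudinal study, but the only assessment described is the baseline questionnaire. A birth recorded later would also follow the baseline symptoms it was meant to predict.

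**A stronger reading to avoid.** A reader might infer that "Emotional impact" simply restates the outcomes, so that distress predicts distress and discrimination is inflated. The article does not support this. It gives a two-word label and no items, and the description of ACT-PNM does not mention it. In a simulation with normally distributed scores and 25% prevalence, assumed correlations of 0.3 to 0.8 with the outcome score give an AUC from this variable alone of about 0.64 to 0.89. The effect thus depends on content that is not shown.

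**Conclusion.** The point holds in two parts. Table 1 contradicts the article's own aims on the role of personality and, followed literally, leaves a named factor out of the models for the second goal. The table also supplies birthweight and preterm birth to whole-sample models, although neither exists for the current pregnancy of women still pregnant. Both parts rest on the text alone.

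The size of the second part rests on assumptions: with complete-case fitting and 20% to 60% pregnant, 168 to 84 of 210 derivation women remain. The documents do not establish that all pregnant women will be dropped or that half the sample will be lost, because neither the fitting method nor the pregnant share is stated. Overlap between "Emotional impact" and the EPDS, GAD-7 or IES-R can be neither confirmed nor excluded.

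**What to change.** 1. Move TIPI to the predictor block of Table 1, so that the prediction models include it and the forward regressions do not treat it as a target.
2. Fit the all-women models without birthweight, preterm birth and delivery complications, and include perinatal stage (pregnant or postpartum) as a covariate.
3. Enter the birth variables only in a postpartum-only model, which also serves the third goal. Delete the duplicate row, and state whether complications means those of pregnancy or of delivery.
4. Before "Emotional impact" is kept as a predictor, check its items for overlap with the EPDS, GAD-7 and IES-R.

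The cost is a change to the table and the analysis wording, and one additional model per outcome. That model is fitted to fewer women, so its estimates will be less precise. No new data are needed.
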